### Aims and objectives

1.To study the effect of mCIMT in addition to conventional therapy on balance (using the Berg Balance Scale (BBS)) and gait (using the Dynamic Gait Index (DGI)) in sub-acute hemiplegic stroke.2.To study the effectiveness of MRP along with conventional therapy on balance (BBS) and gait (DGI) in sub-acute hemiplegic stroke.3.To compare mCIMT and the MRP in improving balance and gait in sub-acute hemiplegic stroke patients along with conventional therapy.

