### Trial design

A single-centre, two arm, parallel group, comparative open labelled superiority trial will be conducted.

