### Sample size calculation

We estimated the sample size using a power analysis with 80% power and 5% Type 1 error for the main variables. The BBS score, in comparison to the difference in mean score pre and post treatment for mCIMT group from baseline to end visits. For the study, we used the previously determined effect size difference in percentage from the RCT.
^
22
^ Formula using mean difference:

$$n1=n2=2\frac{{\left(Z_{\alpha }+Z_{\beta }\right)}^{2}\sigma^{2}}{{\left(\delta \right)}^{2}}$$
Primary Variable (BBS)

Mean ± SD (Pre) result on BBS for mCIMT = 48.8 ± 4.7

Mean ± SD (Post) result on BBS for mCIMT = 52.5 ± 3.5

Difference = 3.7

Pooled std. dev. = (4.7 + 3.5)/2 = 4.1

$$\text{N1}=2^{*}\left[{\left(1.64+0.84\right)}^{2}{\left(4.1\right)}^{2}\right]/{\left(3.7\right)}^{2}=15$$

Considering 10% dropout = 2

Total samples required = 15 + 2 = 17 per group.

Total sample size required = 15

Notations:

$$Z_{\alpha }=\text{1.64 bat 5\% l.o.s. at both sides total 10\% type I error}$$

α=Type I error at 5%

$Z_{\beta }=0.84\;\left(1-\beta \right)=\text{Power at}\;80\%$

σ=std.dev=0.5pooledstd.dev

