### Statistical analysis

Samples taken in accordance with the protocol and recorded on a basis that includes all relevant characteristics. Dataset of outcome variables including demographic, physical, laboratory and vitals information will be collected and tabulated in Excel, and will be analysed using R-Software version 4.3. Demographic variables such as age and gender and physical examination (height, weight, BMI), laboratory parameters (haemoglobin, Erythrocyte Sedimentation Rate (ESR), Liver Function Test (LFT), Kidney Function Test (KFT)), and vitals (respiratory rate, pulse rate, systolic blood pressure, diastolic blood pressure and SpO
_2_ levels) will be collected. Outcome variables such as BBS, DGI, TIS, 10MWT, FRT and FES will be presented over descriptive statistics with categorical tabulation for frequency and percentage, while quantitative measurements with minimum, maximum, mean and standard deviation.

The primary outcome variables will include the BBS for measuring balance and the DGI for measuring gait outcome variables, the secondary outcome variables include the TIS, FRT, 10MWT and FES. Variables as primary and secondary parameters for their measuring assessment at different time visits will be assessed to find the significance in mean at 5% level of significance at P-value < 0.05. Statistical analysis will be performed for hypothesis testing for paired pre and post analysis using a paired t-test for normal data or non-parametric test such as Wilcoxon signed-rank test for non-normal data. Similarly, an unpaired t-test will be used for two independent groups for the change in parameters readings of primary and secondary variables at two different visits.

Data over the outcome variables will be analysed for normality (normal distribution) using Kolmogorov–Smirnov test. If data results over non normal distribution then alternate non parametric test will be used.

Confounding variables will be analysed with generalised linear model to find the random and fixed effects over the outcome variables. Association analysis for finding significance of cofounding parameters will be examined by using Chi-squared test or Fisher’s exact test or by using multi-variant analysis.

Full analysis set for the values of outcome variables will be analysed for the results missing data will be covered with imputation method by calculating the mean and median over the existing data.

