## Discussion

The study’s primary objective is to determine how well mCIMT and MRP work to treat balance and gait issues. These cause a rise in the risk of falling, which further reduces the functional independence of those who had sub-acute stroke. In a previous study, the experimental group received mCIMT for two weeks, while the control group received neurodevelopmental therapy (NDT). The findings showed that mCIMT for lower limb had a superior impact on improving motor function compared with NDT.
^
22
^ Using a randomized controlled trial, the study was done to determine how well the MRP worked to improve balance and upright mobility in sub-acute stroke patients. The results suggested that MRP showed a good impact on post-stroke survivors with the experimental group receiving MRP in addition to conventional physical therapy (RPT) for a duration of five days per week for eight weeks.
^
23
^ Both interventions were found to be beneficial in hemiplegic stroke when compared with a negative control group. But there is dearth of literature reflecting the superiority of either of these interventions when compared with each other. Therefore, our study will compare the two regimes to evaluate which is more successful while looking at the effectiveness of these therapies in sub-acute stroke patients.

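### The sample size enters the mCIMT arm's own pre-post BBS change (3.7 points) as the between-group difference, so 80% power is not established for mCIMT versus MRP

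*Protocol article*

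**What the plan says.** Trial design describes a "two arm, parallel group, comparative open labelled superiority trial". The third item under Aims and objectives is "To compare mCIMT and the MRP in improving balance and gait in sub-acute hemiplegic stroke patients along with conventional therapy". Statistical analysis says that "an unpaired t-test will be used for two independent groups for the change in parameters readings of primary and secondary variables".

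Sample size calculation claims "80% power and 5% Type 1 error for the main variables" and names the effect as "the difference in mean score pre and post treatment for mCIMT group from baseline to end visits". It uses the two-independent-groups formula n1 = n2 = 2(Zα + Zβ)²σ²/δ². The inputs are the mCIMT means before and after treatment in the cited trial, 48.8 (SD 4.7) and 52.5 (SD 3.5). Their difference, 3.7, is entered as δ, and the plain average of the two SDs, 4.1, as σ. The result is 15 per group, or 17 after a 10% dropout allowance. No MRP figure and no between-arm figure appears.

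The Discussion says that both interventions were found beneficial when compared with a negative control. Interventions gives conventional therapy to both groups.

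**The concern.** In a two-group formula, δ is the difference that the trial is meant to detect between its arms. A gain over time within one arm is a different quantity: it contains everything that makes patients improve, including conventional therapy and natural recovery, and the other arm shares much of this. In a comparison of two active treatments, the between-arm difference may be well below either arm's own gain.

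The stated 80% power is the justification for enrolling 34 patients in a superiority comparison. If it rests on the wrong quantity, readers cannot judge what a non-significant result means, and a trial able to detect only large differences is presented as adequately powered.

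**Working it through.** **Inputs.** All from Sample size calculation: pre 48.8 (SD 4.7), post 52.5 (SD 3.5), δ = 3.7, σ = 4.1, Zα = 1.64, Zβ = 0.84, 10% dropout.

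**Reproducing the plan's figure.**
- δ = 52.5 − 48.8 = 3.7; σ = (4.7 + 3.5)/2 = 4.1.
- n = 2 × (1.64 + 0.84)² × 4.1² / 3.7² = 2 × 6.1504 × 16.81 / 13.69 = 15.10, stated as 15.
- 15/(1 − 0.10) = 16.7, so 17 per group and 34 in total.

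The figure reproduces, which confirms that the one-arm change was used as δ. The sum is right; the input is wrong for this comparison.

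**What δ = 3.7 implies.** The between-arm difference is the mCIMT change minus the MRP change. If the mCIMT change is again 3.7, a difference of 3.7 requires an MRP change of 0.

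**What 15 evaluable per arm delivers.** Unpaired t-test with 28 degrees of freedom; power from the noncentral t distribution with noncentrality d/(SD × √(2/15)). For SD 4.1 the standard error is 4.1 × √(2/15) = 1.50. The plan's Zα of 1.64 corresponds to one-sided 5%, although its note reads "l.o.s. at both sides total 10" per cent. The same section claims 5% type I error, and Statistical analysis uses P < 0.05. Both conventions are therefore shown. The differences below 3.7 are assumptions, because the documents give no mCIMT-minus-MRP estimate.

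| Assumed difference (SD 4.1) | Power, two-sided 5% | Power, one-sided 5% |
|---|---|---|
| 3.7 | 67% | 78% |
| 3.0 | 49% | 62% |
| 2.0 | 25% | 37% |
| 1.85 (half of 3.7) | 22% | 33% |
| 1.5 | 16% | 25% |

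The difference detectable with 80% power is 4.35 points two-sided and 3.82 one-sided. With all 17 per arm evaluable it is 4.06 two-sided.

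**SD of change.** The planned test is on change, so the relevant SD is √(4.7² + 3.5² − 2r × 4.7 × 3.5), where r is the pre-post correlation. The documents do not give r; the range 0.5 to 0.8 is assumed.

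| r (assumed) | SD of change | Power for 2 points, two-sided | Detectable at 80%, two-sided |
|---|---|---|---|
| 0.5 | 4.23 | 24% | 4.5 points |
| 0.8 | 2.83 | 46% | 3.0 points |

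A smaller SD helps, but over this range power for 2 points stays below 50%.

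**The case against.** Objectives 1 and 2 are within-arm questions, and a paired test is planned for them, so one might say that 3.7 serves those. This does not stand: the formula is the two-group one, and its SD is not that of paired differences, so the calculation fits neither analysis.

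A fairer objection is that 3.7 could still be the true between-arm difference. The cited trial gave mCIMT for two weeks; this trial gives six weeks of treatment, and the mCIMT gain may be larger. That stands, and it is why the 80% is unestablished rather than shown to be impossible.

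A reader might also infer that 3.7 cannot occur on the scale, because an MRP lead of that size would put its mean at 52.5 + 3.7 = 56.2, above the BBS maximum of 56. This holds only if the mCIMT arm of this trial ends at 52.5. The documents give no expected baseline for these patients, so the argument is conditional and nothing here depends on it.

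Nor is the whole gap between 3.7 and 4.35 due to the choice of δ. The one-sided figure is 3.82, so most of that gap comes from sidedness and the t distribution. The effect of the wrong δ shows in the low power at smaller differences, under either convention.

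Finally, the documents plan no equivalence claim. Misreading a null result is a risk to guard against, not something the plan proposes.

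**Conclusion.** The point holds. A within-arm change has been used as a between-arm difference, and no other section of the protocol corrects this. The 80% power is conditional on mCIMT outperforming MRP by 3.7 points. If mCIMT gains what it gained in the cited trial, that means an MRP arm with no improvement, which conflicts with the protocol's own account of MRP and with the conventional therapy given to both arms.

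For an assumed 2-point difference, power with 15 evaluable per arm is about 25% two-sided (37% one-sided) at SD 4.1, and 24% to 46% two-sided if the SD of change is 4.23 to 2.83. These sizes rest on an assumed difference and an assumed correlation. The error in δ rests on neither. The documents do not support a single corrected sample size, because they give no estimate of the difference between mCIMT and MRP.

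**What to change.** Keep 34 patients and rewrite the sample size paragraph:

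1. Stop presenting 3.7 as the between-group difference; describe it as the mCIMT pre-post change in the cited trial.
2. State what the size delivers, with the assumptions named. For example: with 15 evaluable per arm and a two-sided 5% t-test, the BBS difference detectable with 80% power is about 4.3 points at SD 4.1 (3.8 if one-sided 5%), or about 4.5 to 3.0 points if the SD of change is 4.23 to 2.83 (assumed correlation 0.5 to 0.8). Power for a 2-point difference is about 25% at SD 4.1 (37% one-sided), or 24% to 46% two-sided over that SD range. Fix one sidedness and use it throughout.
3. Base any assumed δ on a between-arm difference in BBS change, with the SD of change. The mCIMT-versus-NDT contrast of the cited trial is only a proxy, because its control was not MRP.
4. Report the between-group difference with its 95% CI as the main result, and state that a non-significant result will not be read as equivalence.

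The cost is a revised paragraph and a less favourable power statement; no patients are added. Protocol amendments says that further changes could not be carried out, but Study status says the trial has yet to begin, so the power statement can be corrected before any data exist.

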### Outcome measures

Time frames at baseline and six weeks later.

*Primary outcomes*
1.
Change in Berg Balance Scale (BBS)
The BBS is a scale with 14 items that is frequently used and is a standardized balance assessment that uses observation to quantitatively assess a patient’s capacity for balance, either statically or while engaging in a variety of planned routine daily tasks. For evaluating static and dynamic balance following a stroke, The inter-rater and intra-rater reliability of BBS for the patients with stroke is 0.97 and 0.98, respectively.
^
15
^ Each item on the scale will be given a score between 0 and 4, giving the patient an overall ranking of 56. A score of 0 means you didn’t complete the project, and a score of 4 means you did it independently.
^
16
^
2.
Change in Dynamic Gait Index (DGI)
The goal of the DGI is to examine dynamic balance while in motion. Eight of the tasks ask participants to keep their balance when walking normally and while doing so in various conditions (such as adjusting their speed, turning their heads to go around obstacles, pivoting around and climbing steps). Each item is given a score between 0 and 3 points, with a maximum score of 24. A higher DGI score indicates greater independent functional mobility. The DGI has been shown to yield ratios of subject variability to total variability with excellent interrater reliability 0.96 and test-retest reliability 0.98.
^
17
^

*Secondary outcomes*
1.
Change in Trunk Impairment Scale (TIS)
The TIS assesses post-stroke trunk movement, static and dynamic sitting balance, and trunk movement coordination. The TIS is used to analyse motor dysfunction of the trunk after a stroke, static and dynamic seated balance and coordination of trunk movement. Overall reliability for clinical care and research in the TIS, 0.96.
^
18
^
2.
Change in Functional Reach Test (FRT)
Utilising a yardstick fastened to the wall at the acromion’s height, functional reach is determined. Functional reach has been shown to exhibit test-retest reliability, interobserver consistency, criterion validity, and concurrent concept validity in earlier investigations. Additionally, it has been demonstrated that in patients undergoing rehabilitation, functional reach is sensitive to clinically significant changes in balance.
^
19
^
3.
Change in 10 Meter Walk Test (10MWT)

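### The SD of 4.1 behind the sample size is not the SD of the BBS change that the between-group test uses, so the stated 80% power has an error of unknown direction

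*Protocol article*

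**What the plan says.** The Sample size calculation section of the protocol article claims "80% power and 5% Type 1 error for the main variables". It uses the formula for two independent means, n per group = 2(Zα + Zβ)²σ²/δ². The inputs come from the mCIMT arm of an earlier randomised trial: "Mean ± SD (Pre) result on BBS for mCIMT = 48.8 ± 4.7", and 52.5 ± 3.5 after treatment. The difference δ is that arm's gain, 3.7. The SD is "Pooled std. dev. = (4.7 + 3.5)/2 = 4.1". With Zα = 1.64 and Zβ = 0.84 the section reports 15 per group, and 17 after a 10% dropout allowance. The notation beneath the calculation describes the SD as "σ=std.dev=0.5pooledstd.dev".

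The Outcome measures section makes change in BBS the first primary outcome, measured at baseline and six weeks. For comparing the arms, the Statistical analysis section says "an unpaired t-test will be used for two independent groups for the change in parameters readings of primary and secondary variables".

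**The concern.** In a two-group formula, σ has to be the within-group SD of the variable that the test compares. Here that variable is each patient's change in BBS. The figures 4.7 and 3.5 describe how much patients differ from one another at one visit. Their average is not the SD of the change, which also depends on how strongly a patient's two scores are correlated.

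The 15 per group and the 80% power therefore rest on the variability of a quantity that the trial does not test. This is a superiority comparison of two active regimens in 34 patients. If it finds no difference, readers will turn to the stated power to judge what that means, and at present that figure cannot tell them.

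**Working it through.** **Inputs.** All are from the Sample size calculation section: SD before 4.7, SD after 3.5, δ = 3.7, Zα = 1.64, Zβ = 0.84. The pre-post correlation rho is not given. It is an assumption here and is varied from 0.3 to 0.8. The SD of change is taken to be the same in both arms.

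**Step 1: reproduce the plan.** 2 × (1.64 + 0.84)² × 4.1² / 3.7² = 2 × 6.1504 × 16.81 / 13.69 = 15.10, printed as 15. So σ = 4.1 was the value used.

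**Step 2: SD of change from the same SDs.** Variance of change = 4.7² + 3.5² − 2·rho·4.7·3.5 = 34.34 − 32.90·rho. Setting this equal to 4.1² = 16.81 gives rho = (34.34 − 16.81)/32.90 = 0.533. Below that value 4.1 is too small, and above it 4.1 is too large.

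**Step 3: isolate the effect of the SD.** δ = 3.7 and the protocol's critical value are held fixed.
- N per group = 2 × 2.48² × variance / 3.7², rounded up.
- Power at 15 per group = Φ(3.7 / (SD × sqrt(2/15)) − 1.645), a normal approximation; 1.645 is the unrounded form of the protocol's 1.64.

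| rho (assumed) | SD of change | N per group | Power at 15 per group |
|---|---|---|---|
| 0.3 | 4.95 | 21.99 → 22 | 66% |
| 0.4 | 4.60 | 19.03 → 20 | 71% |
| 0.5 | 4.23 | 16.07 → 17 | 77% |
| 0.53 | 4.10 | 15.10 (plan prints 15) | 80% |
| 0.6 | 3.82 | 13.12 → 14 | 84% |
| 0.7 | 3.36 | 10.16 → 11 | 91% |
| 0.8 | 2.83 | 7.21 → 8 | 97% |

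Example, rho 0.3: variance 34.34 − 9.87 = 24.47, so SD 4.95. Then 3.7 / (4.95 × 0.365) = 2.05, and Φ(2.05 − 1.645) = 66%.

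**Step 4: detectable difference, which does not depend on 3.7.** At 15 per group with the protocol's Z values it is 2.48 × SD × sqrt(2/15). That gives 4.5 BBS points at rho 0.3 and 2.6 at rho 0.8. With a two-sided 5% t-test the same two values are 5.2 and 3.0.

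**Step 5: two side issues.**
- Root-mean-square pooling gives sqrt((4.7² + 3.5²)/2) = 4.14 and a raw N of 15.4, against 4.10 and 15.1. The way the two SDs were averaged does not matter.
- Read literally, the notation line gives σ = 0.5 × 4.1 = 2.05 and a raw N of 3.8. Step 1 shows that this value was not used.

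**The case against.** The strongest reply is that no loss of power has been shown. If rho exceeds 0.53, 4.1 overstates the SD of change and the sample size is conservative. Nothing in the protocol points to the lower half of the range. The BBS reliabilities of 0.97 and 0.98 that it cites are rater reliabilities, not a six-week correlation, so they do not settle the matter either way. This part stands: a reader might infer that the trial is underpowered because of the SD, and the document does not support that.

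A reader might also recompute power with a two-sided 5% t-test. That gives 66.5% at 15 per group with SD 4.1 unchanged. The fall from about 80% is not an effect of the SD. It comes mainly from the critical value, because the notation glosses 1.64 as "l.o.s. at both sides total 10" percent, and by about 3 points from using t in place of the normal distribution. At rho 0.6 the mixed calculation gives 73%, whereas the SD alone gives 84%. The two effects should be kept apart.

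The notation line invites a stronger reading too, that the sample size should have been about 4 per group. More probably the line is a garbled statement of half the sum of the two SDs, which is exactly 4.1. It changed no result and needs only a correction.

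Finally, the SD is only one weakness of the paragraph. The δ of 3.7 is a pre-to-post gain within one arm, described as "The BBS score, in comparison to the difference in mean score pre and post treatment for mCIMT group from baseline to end visits", and not a difference between mCIMT and MRP. That is also correct: replacing the SD alone would not make the power refer to the planned comparison.

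None of this answers the core point. The formula is for two groups, so it cannot be defended as sizing the within-arm paired test. The protocol itself fixes the between-group test on change, so the choice is not left to an analysis plan. With δ and Z corrected, σ would still be the wrong quantity.

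**Conclusion.** The point holds, with limits. The arithmetic reproduces; the flaw is the choice of input. The stated 80% power and 15 per group do not rest on the SD of BBS change. From the protocol's own SDs, with δ = 3.7 and its critical value held fixed, the SD issue alone puts power anywhere from 66% (rho 0.3) to 97% (rho 0.8) at 15 per group. The N needed ranges from 22 to 8.

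These figures rest on the assumed range of rho, equal SDs of change in both arms and a normal approximation. Because rho is not given, the direction of the error is unknown, and neither underpowering nor overpowering can be concluded. The defect is worth correcting because the study had not begun when the protocol was published and the correction is to the text only.

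**What to change.** Keep the 34 patients and rewrite the sample-size paragraph:

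1. Replace 4.1 with an SD of BBS change. Take it from the cited trial if it is reported there; otherwise derive it as sqrt(4.7² + 3.5² − 2·rho·4.7·3.5) with rho stated and justified.
2. Correct the notation line for σ so that it matches the value used.
3. In the same revision, replace the within-arm 3.7 with a between-group difference in change, and use a Z that matches the stated alpha. Without these the restated power would still not refer to mCIMT against MRP.
4. In place of the unqualified 80%, give the power, or the detectable between-group difference in change, at 15 to 17 per group over rho 0.3 to 0.8.

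The cost is one rewritten paragraph, with no extra patients, visits or procedures. The Protocol amendments section says that further changes could not be carried out, but this one alters nothing in the conduct of the trial. The downside is that the stated power becomes a range, part of which may lie below 80%.

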### Data collection methods

Before group allocation, screening of the participants as per the inclusion and exclusion criteria will be carried out. This will be followed by baseline assessment of the outcome measures as mentioned. All participants will undergo the randomization process and are allocated into either group A or Group B. The intervention will be administered for an hour daily, five days per week for six weeks. The post intervention data for the outcomes will be recorded after the last intervention session day. The data will be compiled and analysed for studying the results. The study interventions will be administered by the principal investigator under the supervision of the guide throughout the duration of the study. The patients will be instructed and reminded of the sessions in advance through messages sent to their mobile phones so that adherence to the study is ensured. Furthermore, if the patient misses their sessions due to any reason, the standby days from the week will be utilized such that the patient receives a total of 30 sessions of intervention in the six week duration.

As per in the sample size calculation we have given a 10% dropout rate so that it does not interfere with the results of our study.

The data collection forms can be found as
*Extended data.*
^
24
^

